#### Sample Size and Power Calculations

Sample size calculations are based on the pilot study on 28 patients [20], in which 80% of the participants treated with PRP experienced an improvement in their symptoms. Assuming a difference of 30% between PRP and normal saline at 12 months, an α risk of 5%, and a power of 80%, a sample size of 31 participants for each group is required. Assuming that 10% of the participants withdraw or are lost to follow-up, a sample size of 34 participants for each group is required or a sample size of 68. The pilot study used subjective symptom improvement as its primary outcome, whereas this trial’s primary outcome is the LS clinical score, an objective physician-rated measure. Although these outcomes differ, symptom improvement in the pilot study was used as a surrogate to estimate a conservative effect size for this study, given the lack of prior data on LS clinical score changes with PRP. This study will also evaluate secondary outcomes, including subjective symptom scores, allowing for comparisons between subjective and objective measures.

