**Methods:**

This is a protocol for a 12-month, single-center, parallel-group, double-blind, randomized controlled trial evaluating the efficacy of PRP for LS compared to saline. Adult female patients with biopsy-proven LS who are otherwise in good health but are nonresponders to topical steroid treatment prior to inclusion are eligible for the trial. A total of 68 participants will be randomly allocated via a random number generator to receive either PRP or saline injections to areas of the vulva with LS. All participants will be blinded to the intervention received. Participants will be followed up with assessments of clinical LS signs, subjective symptom scores, and quality of life questionnaires by blinded assessors at 4 timepoints: baseline, 6 weeks, 6 months, and 12 months. The primary outcome is the clinical scoring system for LS—the total LS score.

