### Statistical Analysis

All analyses will be conducted using SPSS software (IBM Corp). We will perform analyses using the intention-to-treat principle. Outcomes will be compared within groups over time and between groups at baseline, 6 weeks, 6 months, and 12 months. Baseline characteristics will be summarized using descriptive statistics, and a comparison of the 2 treatment arms will be assessed by 1-way analysis of variance or 1-sided *t* test for continuous variables or nonparametric alternatives if data are not normally distributed. The Shapiro-Wilk test will be used to assess if data are normally distributed. For all tests, a significant level of α=5% is applied. The analysis of changes compared to the baseline will test the null hypothesis that there is no difference between the 2 timepoints. Further analyses between the groups will test the null hypothesis that there are no differences between the 2 groups at one timepoint. Missing value analysis will be performed, and missing values will be imputed using expectation maximization. Analyses will be conducted in line with the intention-to-treat principle, which will be compared to per-protocol analyses.

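### The planned 31 per group gives 80% power only with a one-sided 5% test, which the sample size paragraph does not declare; at two-sided 5% the power is about 71%

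*Protocol article*

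**What the plan says.** The Sample Size and Power Calculations section starts from a pilot study of 28 patients, "in which 80% of the participants treated with PRP experienced an improvement in their symptoms". It continues: "Assuming a difference of 30% between PRP and normal saline at 12 months", with "an α risk of 5%, and a power of 80"%, "a sample size of 31 participants for each group is required". It then allows for 10% loss and arrives at 34 per group, 68 in all. No sidedness is attached to the alpha and no response rate is given for saline.

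The Statistical Analysis section sets one level throughout: "For all tests, a significant level of α=5% is applied". Sidedness appears once, in the sentence on baseline characteristics: "a comparison of the 2 treatment arms will be assessed by 1-way analysis of variance or 1-sided *t* test for continuous variables". Later in the section, the between-group null is that the two groups do not differ at a given timepoint, with no direction specified.

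The Background section of the Introduction twice describes the trial as adequately powered, and the Limitations section says it has the power to detect a difference between groups. The Results section reports that recruitment has ended with 34 participants in total.

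**The concern.** A reader who meets an unqualified 5% alpha in a two-arm superiority trial will take it as two-sided. On that reading the stated inputs do not lead to 31 per group, and the stated 80% power is not delivered. A one-sided 5% test corresponds to a two-sided 10% test when the effect lies in the expected direction, so the undeclared choice is material.

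What is at stake is how the trial is reported. The results paper will quote the planned size and interpret a recruitment shortfall against it. If the target is taken as a two-sided 80% design, the shortfall looks smaller than it was, and a null result looks more informative than it is.

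**Working it through.** **Inputs.** From Sample Size and Power Calculations: PRP rate p1 = 0.80; difference 30%; alpha 5%; power 80%. From Randomization and Blinding: 1:1 allocation. Assumption: the 30% is an absolute difference, so the saline rate is p2 = 0.80 − 0.30 = 0.50.

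**Formula.** With p̄ = (p1 + p2)/2 = 0.65,

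n per group = [z_α √(2p̄(1−p̄)) + z_β √(p1(1−p1) + p2(1−p2))]² / (p1 − p2)²

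Here √(2 × 0.65 × 0.35) = √0.455 = 0.6745, √(0.16 + 0.25) = √0.41 = 0.6403, z_β = 0.8416 and (p1 − p2)² = 0.09.

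**Reproducing the plan's figure: one-sided 5% (z_α = 1.645).** (1.645 × 0.6745 + 0.8416 × 0.6403)² / 0.09 = (1.1095 + 0.5389)² / 0.09 = 30.19, so **31 per group**. This matches the article.

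**Two-sided 5% (z_α = 1.960).** (1.3221 + 0.5389)² / 0.09 = 38.48, so **39 per group**.

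**Does another formula give 31 with a two-sided test?**

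| Variant (80% vs 50%) | One-sided 5% | Two-sided 5% |
|---|---|---|
| Pooled variance under the null (above) | 31 | 39 |
| Unpooled variance | 29 | 36 |
| Arcsine | 30 | 38 |
| Pooled variance in both terms | 32 | 40 |
| Continuity-corrected | 37 | 45 |

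No. The two-sided results run from 36 to 45.

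**Does another reading of the 30% give 31?** A relative reduction gives a saline rate of 0.80 × 0.70 = 0.56, and the pooled formula then needs 46 one-sided or 59 two-sided. A two-sided test comes near 31 with other pairs 30 points apart, such as 90% against 60% (32 per group), but these contradict the stated 80%.

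**Power for 80% vs 50%.** Power = Φ([0.30 √n − z_α × 0.6745] / 0.6403).

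- n = 31, one-sided: (1.6703 − 1.1095)/0.6403 = 0.876, power 80.9%.
- n = 31, two-sided: (1.6703 − 1.3221)/0.6403 = 0.544, power 70.7%. Exact enumeration of the chi-square test gives 71.4%.
- n = 34 (no loss), two-sided: 74.8%.
- n = 39, two-sided: 80.5%.

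**Two-sided requirement with 10% loss.** 38.48/0.9 = 42.8, so 43 per group; or, rounding up first, 39/0.9 = 43.3, so 44 per group. That is 86 to 88 in all, against 68 planned.

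**The case against.** The strongest defence is that 31 is not a miscalculation. It follows exactly from the stated inputs under a one-sided 5% test, and the only sidedness named anywhere in the article is one-sided. A null of no difference does not fix the alternative, since one-sided tests are often written with the same null. All of this stands. A reader might infer that the plan is two-sided and that 31 is therefore an arithmetic error, but the article never says two-sided. It does not establish one-sided either: the one-sided t test is named for baseline characteristics, beside an analysis of variance whose F test has no direction. What survives is that the 80% power depends on a choice that the sample size paragraph does not declare and the analysis section does not settle.

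A reader might also infer that the loss allowance is wrong, because 31/0.9 = 34.4 would round up to 35, where the article has: "Assuming that 10% of the participants withdraw or are lost to follow-up, a sample size of 34 participants for each group is required". That does not hold. The unrounded requirement is 30.19, and 30.19/0.9 = 33.5, which rounds up to 34. After 10% loss, 34 × 0.9 = 30.6 still exceeds 30.19. The difference is a rounding convention, so 34 per group and 68 in all are consistent with the one-sided calculation.

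Two limits on the size of the point are also fair. The 71% is power for a binary symptom response, whereas the primary outcome is change in a 0 to 12 clinical score; the article openly calls the symptom figure a surrogate. Neither 80% nor 71% is therefore the power of the primary comparison. And with recruitment closed at 34 in total, no correction alters what was done. Neither limit removes the need to state correctly the figure on which the article's claims of adequate power rest.

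**Conclusion.** Wrong as written. Under the usual two-sided meaning of a 5% alpha, 31 per group does not give 80% power for 80% against 50%: it gives about 71%, and 39 evaluable per group are needed. The stated 31 with 80% power is right only for a one-sided 5% test, which the paragraph does not mention.

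The conclusion rests on the absolute reading of the 30% difference, with a derived saline rate of 50%. The relative reading fits worse (46 one-sided, 59 two-sided), so the assumption does not create the discrepancy. All power figures refer to the binary surrogate used for planning.

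**What to change.** Correct the text only:

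- In Sample Size and Power Calculations, state that the calculation uses a one-sided 5% alpha and an assumed saline rate of 50%. Add that at two-sided 5% the power with 31 per group is about 71%, and that 80% would need 39 evaluable per group (43 to 44 per group with 10% loss, depending on rounding).
- In Statistical Analysis, state the sidedness of the between-group tests and make it consistent with that paragraph, including the baseline sentence.
- In Background and Limitations, qualify the statements that the trial is adequately powered, so that they say for which test and alpha this was meant.

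Leave 34 per group and 68 in all as the planned figures. The cost is a few sentences and a less favourable stated power; nothing in recruitment, allocation or data collection changes.

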### Statistical Analysis

All analyses will be conducted using SPSS software (IBM Corp). We will perform analyses using the intention-to-treat principle. Outcomes will be compared within groups over time and between groups at baseline, 6 weeks, 6 months, and 12 months. Baseline characteristics will be summarized using descriptive statistics, and a comparison of the 2 treatment arms will be assessed by 1-way analysis of variance or 1-sided *t* test for continuous variables or nonparametric alternatives if data are not normally distributed. The Shapiro-Wilk test will be used to assess if data are normally distributed. For all tests, a significant level of α=5% is applied. The analysis of changes compared to the baseline will test the null hypothesis that there is no difference between the 2 timepoints. Further analyses between the groups will test the null hypothesis that there are no differences between the 2 groups at one timepoint. Missing value analysis will be performed, and missing values will be imputed using expectation maximization. Analyses will be conducted in line with the intention-to-treat principle, which will be compared to per-protocol analyses.

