### Outcome Measures

#### Primary Outcome Measure

The primary outcome of this study was to compare the efficacy of PRP and saline injections by evaluating the change in the LS clinical score across groups at 3 timepoints: 6 weeks, 6 months, and 12 months (Table 1). The clinical scoring system for LS is an objective, validated, physician-administered assessment measuring the severity of vulvar LS [18]. Six clinical characteristics are graded on a 3-point Likert scale with grade 0 as normal, grade 1 as moderate changes, and grade 2 as severe changes. The clinical characteristics are erosion, hyperkeratosis, fissures, agglutination, stenosis, and atrophy. Scores range from a minimum of 0 to a maximum of 12; a score ≥4 identifies LS with a probability of >90% in conjunction with the participant experiencing intractable symptoms such as pruritus, dyspareunia, soreness, or burning [22].

**Table 1 table1:** Clinical scoring system for vulvar lichen sclerosus.

Clinical characteristic	Grade 1 (moderate)	Grade 2 (severe)
Erosion	1-2 small erosions, almost not macroscopically visible	Macroscopically visible and/or >2 or confluent lesions
Hyperkeratosis	≤10% vulva and perineum affected	>10% vulva and perineum affected
Fissure	Rhagades affecting the posterior introitus	Generalized vulvar rhagades
Agglutination	Partially affecting preputium clitoridis and labial minora	Complete agglutination of both labia minora or majora
Stenosis	Narrowing of introitus, which could still be passed by 2 fingers	Narrowing, which could be passed by less than 2 fingers
Atrophy	Shrinking of labia and clitoris	Labia minor and clitoris were no longer visible

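### The only between-arm test named for continuous data pairs a two-sided test with a one-sided one at the same 5% level, against an undirected null; the sidedness must be fixed and the sample size restated to match

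*Protocol article*

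**What the plan says.** All of this is in the protocol article.

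- **Test.** Statistical Analysis, in a sentence that opens with baseline characteristics: "a comparison of the 2 treatment arms will be assessed by 1-way analysis of variance or 1-sided" *t* test for continuous variables, with unnamed nonparametric alternatives if the data are not normal. It gives no rule for choosing between ANOVA and the *t* test, and no direction for the one-sided test.
- **Level.** "For all tests, a significant level of α=5% is applied". The level is not halved for a one-sided test.
- **Null hypothesis.** "Further analyses between the groups will test the null hypothesis that there are no differences between the 2 groups at one timepoint". This has no direction.
- **Comparisons.** "Outcomes will be compared within groups over time and between groups at baseline, 6 weeks, 6 months, and 12 months". The primary outcome is assessed by "evaluating the change in the LS clinical score across groups at 3 timepoints: 6 weeks, 6 months, and 12 months" (Primary Outcome Measure).
- **Sample size.** With 80% improvement on PRP in the pilot, a 30% difference, α of 5% and power of 80%, "a sample size of 31 participants for each group is required" (Sample Size and Power Calculations). Sidedness, control rate and formula are not given.

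**The concern.** The two tests joined by the word *or* look interchangeable but are not. In a two-arm trial the ANOVA P value is the two-sided *t*-test P value, which is twice the one-sided P when the effect lies in the tested direction. At a common 5% level the text therefore permits two thresholds for the same data. One of them does not fit the undirected null, and no directional alternative is stated or justified anywhere.

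If the sentence reaches the outcomes, it affects how strong the evidence behind a treatment claim has to be. A one-sided test aimed at benefit also could not show PRP to be worse than saline, although the Study Aims cover safety as well as efficacy.

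**Working it through.** **1. ANOVA against the *t* test.** With two groups F = t², so the ANOVA P equals the two-sided P. In a simulated example with 31 per arm, F = t² = 20.82, the ANOVA P was 2.55 × 10⁻⁵ and the one-sided P was 1.27 × 10⁻⁵, a ratio of 2.000. In the opposite direction the one-sided P is 1 − P/2, here above 0.9999, so the factor of two holds only in the tested direction. With 60 degrees of freedom the critical t is 1.67 one-sided and 2.00 two-sided.

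**2. False-positive rates per comparison.** Theory, with 100,000 null simulations at 31 per arm in brackets:

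| Rule | In the tested direction | Total |
|---|---|---|
| ANOVA (two-sided 5%) | 2.5% (2.45%) | 5% (4.96%) |
| One-sided *t* test at 5% | 5% (4.89%) | 5% (4.89%) |
| Either test, significant if one is | 5% | 5% + 2.5% = 7.5% (7.4%) |

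The last row would apply only if the choice were left open until the data were seen.

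**3. The plan's own 31 per group.** Inputs from the sample size section: PRP 0.80, difference 0.30, α 0.05, power 0.80. Assumption: the 30% is absolute, so the control rate is 0.50 and the mean rate is 0.65.

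Pooled formula: n = [z_α √(2 × 0.65 × 0.35) + z_β √(0.80 × 0.20 + 0.50 × 0.50)]² / 0.30², with √0.455 = 0.6745, √0.41 = 0.6403 and z_β = 0.8416.

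- One-sided, z_α = 1.645: (1.1095 + 0.5389)² / 0.09 = 30.19, so **31**. This reproduces the stated figure.
- Two-sided, z_α = 1.960: (1.3221 + 0.5389)² / 0.09 = 38.48, so **39**.

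Other formulas for the same rates:

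| Formula | One-sided | Two-sided |
|---|---|---|
| Pooled | 31 | 39 |
| Pooled, continuity correction | 37 | 45 |
| Unpooled | 29 | 36 |
| Arcsine | 30 | 38 |

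If the 30% is read as relative (0.80 against 0.56), the pooled formula gives 46 one-sided and 59 two-sided, and neither matches 31.

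**4. Power at the stated size.** Power = Φ[(0.30 √n − z_α × 0.6745) / 0.6403].

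- n = 31, one-sided: Φ[(1.6703 − 1.1095) / 0.6403] = Φ(0.876) = 80.9%.
- n = 31, two-sided: Φ[(1.6703 − 1.3221) / 0.6403] = Φ(0.544) = 70.7%.

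For 80% power two-sided, 39 per group is needed. With 10% loss, 39 / 0.9 = 43.3, so 44 per group or 88 in total, against the planned 68.

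**5. At the recruited size.** The Results section reports 34 participants in total. Assuming 17 per arm and no loss, the same formula gives 58% one-sided and 45% two-sided.

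The power figures in steps 4 and 5 describe the planning comparison of two improvement proportions. They are not the power of a *t* test on change in the LS score.

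**The case against.** The strongest reply is that the sentence concerns baseline balance only. It opens with baseline characteristics, and the between-group comparison of outcomes comes later in the section, with an undirected null and no one-sided wording. On that reading no efficacy claim is affected, and the outcome test may sit in an analysis plan that is not shown. This stands in part: the reach to outcomes is an inference. It does not rescue the sentence, because chance imbalance at baseline has no expected direction and a one-sided test there serves no purpose.

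Second, the match at 31 is supportive rather than conclusive. It depends on an absolute difference, pooled variance and no continuity correction, and other one-sided formulas give 29, 30 and 37. A one-sided calculation for proportions also does not fix the sidedness of a later test on a 0 to 12 score. All of that stands. What remains is that none of the two-sided formulas tried comes below 36, so a slip of *1-sided* for *2-sided* is less likely than it would otherwise be.

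Third, the primary score is a sum of six 0 to 2 grades and may go down the nonparametric branch, whose sidedness is not stated. That is a reason for the correction to cover that branch as well.

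Three stronger inferences are tempting but unsupported. The document does not say that the test is chosen after the data are seen; it only omits a selection rule. It does not say that the one-sided test favours PRP. And a single prespecified one-sided test at 5% does not double the total type I error: only the rate in the tested direction doubles.

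**Conclusion.** The wording needs correcting on either reading. It offers two tests with different error rates as alternatives at one level, and the one-sided option contradicts the undirected null in the same section.

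The effect on efficacy is conditional. If the sentence governs outcomes, which is likely but not stated, the false-positive rate in the tested direction is 5% rather than 2.5% per comparison, and results in that direction with a two-sided P between 0.05 and 0.10 could be declared significant. Results in the opposite direction would not gain. A reader might conclude that the efficacy analysis is definitely one-sided in favour of PRP; the text does not establish that.

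The sample size is part of the same point. Assuming an absolute 80% against 50% and the pooled formula, 31 per group gives about 81% power one-sided and 71% two-sided, so the stated 80% is not met once the tests are two-sided. With 34 recruited in all, borderline results are plausible and the choice of test could decide the conclusion.

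**What to change.** In Statistical Analysis, delete the one-sided option and state that all between-arm comparisons of outcomes, including the nonparametric alternatives, are two-sided at the 5% level and reported with 95% confidence intervals. Any baseline tests that are kept should be two-sided as well; dropping baseline P values altogether is a reporting preference and not needed for this correction.

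In Sample Size and Power Calculations, state that 31 per group corresponds to a one-sided 5% level for 80% against 50%, that two-sided power at that size is about 71%, and that 39 per group would be needed for 80%. Recruitment has ended, so this is a disclosure and not a call for more participants. The article says that analysis was under way in 2025, so the change should be dated and, if still possible, made before outcomes are compared by arm.

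The cost is a sentence in each section and a stated power that looks less favourable.

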#### Secondary Outcome Measures

Secondary outcome measures will compare changes in the subjective assessment scores over time within each group and between groups. Participants will complete the Australian Pelvic Floor Questionnaire and Dermatology Life Quality Index at each assessment appointment to evaluate changes in the subjective disease burden. The Australian Pelvic Floor Questionnaire is a validated self-administered questionnaire assessing pelvic floor symptoms, including bladder, bowel, prolapse, and sexual function symptoms, as well as symptom severity and impact on quality of life [23]. The Dermatology Life Quality Index is a validated tool assessing quality of life impairment for people experiencing inflammatory skin conditions, and a change in the score of at least 4 points is considered clinically significant [24]. A Visual Analogue Scale will be presented to participants at each assessment to record the severity of their symptoms. Participants will be asked to indicate their level of distress in relation to 2 symptoms: pruritus and dyspareunia.

The additional secondary outcomes are safety and adverse events of receiving the treatment. Autologous PRP has an advantageous safety profile due to the utilization of the patient’s own blood, which minimizes the risk of adverse events or autoimmune reactions [25]. In a pilot study undertaken by the principal investigator, all participants (n=28) reported minimal to mild pain in the 24 hours following the procedure [20]. There were no reported cases of infection, bleeding, hematoma, or other adverse effects. Adverse events will be monitored immediately after receiving the treatment, and at each assessment appointment, participants will be asked if they experienced any adverse events in the preceding period. Any adverse effects will be recorded and reported to the ethics committee.

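### The stated hypotheses do not match the primary outcome: no test they set out clearly uses the baseline LS score to compare PRP with saline

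*Protocol article*

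**What the plan says.** The Primary Outcome Measure section of the protocol article describes "evaluating the change in the LS clinical score across groups at 3 timepoints: 6 weeks, 6 months, and 12 months". The Secondary Outcome Measures section makes a similar commitment for the patient-reported scores, to "compare changes in the subjective assessment scores over time within each group and between groups".

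The Statistical Analysis section gives a general plan: "Outcomes will be compared within groups over time and between groups at baseline, 6 weeks, 6 months, and 12 months". It then states two null hypotheses.

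- For change: "The analysis of changes compared to the baseline will test the null hypothesis that there is no difference between the 2 timepoints".
- For the arms: "Further analyses between the groups will test the null hypothesis that there are no differences between the 2 groups at one timepoint".

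The tests named are given in the sentence on baseline characteristics, where "a comparison of the 2 treatment arms will be assessed by 1-way analysis of variance or 1-sided" t test, or by nonparametric alternatives. The significance level covers everything: "For all tests, a significant level of α=5% is applied".

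The article states no difference in change between arms, no baseline-adjusted model and no group-by-time term. The baseline LS score is collected (Baseline Assessment section).

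**The concern.** The outcome section promises a comparison of change between arms. The hypothesis about change has no arm in it, and the hypothesis about arms has no change or baseline in it. Read literally, neither tests the stated outcome.

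Two things are at stake.

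- **Precision.** The Results section reports 34 participants recruited, against 68 planned. Three of the six graded items (agglutination, stenosis, atrophy) describe vulvar architecture, and the Abstract calls architectural change irreversible. Stable differences between patients are therefore plausible, and a comparison that ignores baseline leaves them in the error term.
- **Interpretation.** Within-arm tests are planned inferential tests at 5%. Both arms may improve for reasons unrelated to PRP, so a significant change in one arm and not in the other says little about the difference between them.

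**Working it through.** **The plan's own figure.** The Sample Size section states 31 per group. With 80% versus 50% (the 50% follows from 80% minus 30 points), n = [z(α)·√(2 × 0.65 × 0.35) + z(power)·√(0.80 × 0.20 + 0.50 × 0.50)]² / 0.30².

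- One-sided 5%: (1.645 × 0.6745 + 0.842 × 0.6403)² / 0.09 = 30.2, so 31.
- Two-sided 5%: (1.960 × 0.6745 + 0.842 × 0.6403)² / 0.09 = 38.5, so 39.

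The stated 31 is thus a one-sided calculation for a symptom-responder proportion. It contains no SD for the LS score, so it cannot size the present point.

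**Outcome against hypotheses.**

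| Section | Quantity | Arms compared? | Baseline used? |
|---|---|---|---|
| Primary Outcome Measure | Change in LS score | Yes | Yes |
| Statistical Analysis, change hypothesis | Two timepoints | No | Yes |
| Statistical Analysis, group hypothesis | Groups at one timepoint | Yes | Not stated |

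The general plan lists baseline among the between-group visits. A change from baseline does not exist at baseline, so the natural reading of the group comparison is the score at each visit.

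**Cost in precision.** Inputs:

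- 17 per arm: 34 recruited, 1:1 allocation, no losses assumed.
- Effect 0.76 SD: an assumption. It equals the logit conversion of 80% versus 50%, ln(4) × √3/π = 0.76.
- Correlation r between baseline and follow-up score: an assumption, 0.3 to 0.7.
- Two-sided 5% t test with 32 df. Taking one df off for the covariate moves power by less than 0.1 percentage points.

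Residual variance relative to the follow-up score is 1 for the unadjusted score, 1 − r² for ANCOVA and 2(1 − r) for unadjusted change. The noncentrality is (0.76/√variance) × √(17/2), with √(17/2) = 2.915.

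| Analysis | r | Variance | Noncentrality | Power |
|---|---|---|---|---|
| Follow-up score | any | 1.00 | 2.22 | 57.5% |
| ANCOVA | 0.3 | 0.91 | 2.32 | 61.5% |
| ANCOVA | 0.5 | 0.75 | 2.56 | 69.9% |
| ANCOVA | 0.7 | 0.51 | 3.10 | 85.3% |
| Change | 0.3 | 1.40 | 1.87 | 44.3% |
| Change | 0.5 | 1.00 | 2.22 | 57.5% |
| Change | 0.7 | 0.60 | 2.86 | 79.2% |

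The sample-size equivalent of ANCOVA is 1/(1 − r²): 1.10, 1.33 and 1.96, that is 10%, 33% and 96% more patients. Unadjusted change beats the follow-up score only when 2(1 − r) < 1, so when r > 0.5.

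**Within-arm tests when there is no treatment difference.** Both arms improve by the same g SDs of change. Let p be the power of a two-sided 5% paired t test with 17 patients (noncentrality g√17). PRP alone is significant with probability p(1 − p).

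| g | p | PRP alone | Exactly one arm |
|---|---|---|---|
| 0.3 | 0.214 | 16.8% | 33.6% |
| 0.4 | 0.341 | 22.5% | 45.0% |
| 0.5 | 0.491 | 25.0% | 50.0% |
| 0.6 | 0.642 | 23.0% | 46.0% |
| 0.8 | 0.872 | 11.2% | 22.3% |

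A two-sided 5% test between arms would favour PRP wrongly in 2.5% of such trials.

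**The case against.** Several stronger readings are tempting, and the documents do not carry them.

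- **That the plan never compares change between arms.** The Statistical Analysis section does not use the term raw score. The group hypothesis follows directly after the one on change, so it could mean comparing changes visit by visit. The inclusion of baseline among the visits argues against this without settling it. What stands is that the hypotheses as written do not clearly test the defined outcome. A condensed article may leave the choice of covariates to a fuller document, so the absence of ANCOVA alone would be no finding. The mismatch between stated outcome and stated hypotheses is one.
- **That the between-arm comparison is biased.** It is not. Comparing randomised arms at follow-up is valid and keeps its type I error. The chance of a baseline imbalance above 0.5 SD at 17 per arm is about 14%, but that is not an error rate, because the test already allows for it.
- **That efficacy will be claimed from a significant change in PRP and none in saline.** No section says so, and between-group comparison is planned throughout. Within-group change is a declared secondary comparison.
- **That half of such trials would mislead in favour of PRP.** The 50% is the maximum of 2p(1 − p) and counts saline alone being significant. PRP alone peaks at 25%.
- **That regression to the mean in the LS score is certain.** Entry is on symptoms, with no LS score threshold. The stable architectural items also argue against large spontaneous change.

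The size depends on assumptions too. At r = 0.3 the gain is small. A one-sided 5% test would have unadjusted power of 70%. At the planned 31 per arm, two-sided, power would be 84% unadjusted and 92.5% with ANCOVA at r = 0.5.

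**Conclusion.** The concern holds as a mismatch between the outcome and the hypotheses, with a loss of precision rather than bias. The stated tests separate change from arm, and no between-arm test is clearly set out that uses the baseline score. With the 34 participants recruited, ignoring baseline costs the equivalent of 10% to 96% more patients for correlations of 0.3 to 0.7. Within-arm tests cannot fill the gap, since with equal true improvement of 0.3 to 0.6 SD of change PRP alone would be significant in about 17% to 25% of trials. These figures rest on a 0.76 SD effect, 17 per arm, two-sided 5% tests and correlations that the documents do not give. The direction of the gain does not depend on them, provided that baseline and follow-up scores are appreciably correlated.

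**What to change.** State one primary contrast: the 12-month LS score by arm, adjusted for the baseline LS score, with a 95% CI. Either ANCOVA or a repeated-measures model with baseline, visit, arm and arm-by-visit terms will serve, with the 12-month contrast read from the latter. Twelve months is the time at which the Sample Size section places its assumed difference. Use the same model for the Dermatology Life Quality Index, the visual analogue scales and the pelvic floor questionnaire. Say that within-arm changes are descriptive and not evidence of efficacy. Do not substitute unadjusted change, which would lose precision if the correlation is below 0.5.

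No new data are needed, and SPSS fits these models. The cost is procedural: the article says that analysis is being done in 2025, so the change needs a dated amendment before allocations are revealed. If they are already known to those analysing the data, report the adjusted analysis openly as a post hoc change.
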